### Allocation

The biomaterials laboratory clinical research unit (URB2I-EA4462, Faculty of Dentistry, Paris Descartes University) is responsible for the randomization.

#### Sequence generation

Treatment allocation is attributed by minimization and takes into account the following main prognostic factors: operator (two teams: prosthodontics practitioner/surgeon), smoking habit (<10 cigarettes/day or ≥ 10 cigarettes/day), and periodontal disease evolution (< or ≥ half the radicular height). To reduce predictability, 30 % randomness is included into the minimization algorithm (this method was chosen to minimize imbalance and predictability, according to the Hermes simulation software [44]).

#### Allocation concealment mechanism and implementation

The patient has to be included/registered online with the RandoWeb® software (AP-HP, Paris, France) before complete denture delivery, so all data are recorded prospectively without inclusion being influenced by the allocation result.

During the surgery, just after extraction of the last teeth, the allocation result can be obtained online by the surgeon if the patient has been included/registered online beforehand. The treatment arm is then attributed (control group: conventional surgery without osseous filling; experimental group: alternative surgery with socket filling). Operators have access only to the last inclusion result in the randomization table, to limit predictability.

[name] conceived the minimization algorithm and [name] implemented it into the RandoWeb software.

### Blinding

The study is described as a double-blind trial (patients and outcome assessors). Surgeons and prosthodontists cannot be blinded, but radiologists perform measurements blindly. Operators do not communicate with the patient about the treatment to ensure independent radiologist measurements of ridge height and width.

### Data collection

Investigators will use a CRF to record all items required for the outcomes analysis. A clinical research assistant visits the investigation center every 6 months to monitor the collection of data (by checking that no CRF field is incomplete) and to assess the quality (by comparing the data in the medical record, the data entered through the online inclusion and randomization software RandoWeb (AP-HP, Paris; http://randoweb.aphp.fr), and the data in the CRF).

Two independent calibrated operators, with blinding to the treatment arm, perform radiologic measurements.

The data are transmitted to an adjudication committee to harmonize the collection standardization and data evaluation. This committee consists of a radiologist, a prosthodontist, and a surgeon. It focuses on the primary outcome.

Participant retention should not be difficult for the first two radiological exams because routine appointments for maintenance usually continue for up to 2 months, when a second CBCT appointment occurs. Patients are advised that denture maintenance will occur 1 year after placement at the time of the third radiologic exam. The clinical research assistant calls 1 month before the date of the third CBCT to make the appointment. In case of five unsuccessful calls, two registered letters with acknowledgement of receipt are sent.

### Data management

Data are recorded on the CRF by investigators and evaluators. All fields must be completed.

Patient data are anonymous because patients will be identified by their inclusion number (the first letter of their first and last name and date of birth only will be registered on the CRF).

For statistical analysis, the data are recorded in an Excel spreadsheet before being analyzed with Stata 12.

### Statistical methods

The data will be analyzed by an independent statistician ([name], in collaboration with the Henri Mondor Hospital Clinical Research Unit). The unit of analysis will be the extraction site (a maximum of six teeth will be extracted per patient). The demographic and clinical characteristics of the patients, the alveolar bone, and the extracted teeth will be described for both treatment arms with the usual statistics: mean and SD or median and interquartile ranges for quantitative variables and number of subjects and percentages for the qualitative variables [53]. The analyses will be performed according to the intent-to-treat principle.

#### Primary outcome analysis

The main analysis will compare the final loss (D365-D10) of bone ridge height between the experimental and control group. This main analysis will be adjusted on the following prespecified variables: operator team, smoking habit, periodontal disease evolution, and age and sex of the patient. A linear mixed model (probably marginal) will be used to account for the correlation between the different bone ridge height values in the same patient (level 1 will be the extraction site, and level 2 will be the patient; level 3 will be the investigator team, if necessary). The main analysis will take into account missing outcome data by multiple imputation, with the assumption that data are missing at random. We will report the unadjusted analysis as well; mean final loss of bone ridge height will be compared between the experimental and control group by Mann-Whitney test. All *p* values will be two-tailed, with a significance level of 0.05.

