#### Post-operative

Post-operative procedures are as follows:The patient is instructed not to remove the immediate denture for 48 h.At D2, the prosthodontic specialist cautiously removes the denture and cleans it. In this way, the specialist controls the healing. The patient is shown how to replace and remove the denture.Maintenance appointments are scheduled at D4, D7, D15, and each week as long as necessary to ensure comfort with the new denture. During these appointments, mucosal healing is checked, and routine adjustments to the denture base and occlusion are performed.Baseline measurements of the crestal ridge are taken at D10 with CBCT. Intermediary and final measurements are scheduled at 3 and 12 months.

No special medical concomitant care or interventions are prohibited during the trial.

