### Outcomes

The primary outcome is to compare overall (the mean of all extraction sites) mean bone ridge height loss (D365–D10) at 1 year after maxillary immediate complete denture placement with or without bone substitution. A quantitative evaluation method using CBCT was designed.

The secondary outcomes are as follows:To compare mean bone ridge height loss, site by site (central incisor, lateral incisor, and canine), with the same technique after 3 months (D90-D10) and after 1 year (D365-D10)To compare mean bone ridge width, overall and site by site, with the same technique after 3 months (D90-D10) and after 1 year (D365-D10).

CBCT data collection and ridge measurements are performed in an independent specialized radiology clinic. For the study purposes, a CBCT unit (NewTom VGi QR s.r.l.©, Verona, Italy), with a 7.5 × 12-cm field, was selected. CBCT data are collected at D10, D90, and D365. The volume CT dose index ranges from to 2 to 4 mGy per examination, according to the patient morphology.

An original protocol was developed to perform reproducible measurements and to compare ridge resorption in the two treatment arms. Bone height and width are measured on CBCT reconstructions by using a radio-opaque denture duplicate specifically designed for the study purposes.

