### Sample size

The number of participants needed to achieve study objectives was estimated to be 34. From a literature review [10, 11, 24–26], we estimated that the average 1-year resorption would be 3 mm in the control group (SD = 1.5 mm) and that 2 mm of bone preservation in the test group would be clinically significant. With an alpha risk of 5 % and a beta risk of 10 %, 12 patients per group were required. Because two operator groups would be involved, extra variability could be expected. No ICC was reported in reports identified by our literature review, so ICC 0.02 was chosen (coefficient obtained in a previous clinical study conducted by our research unit [43]). Based on this ICC, the sample size was increased, and 29 patients (12 × 2 × (1 + (11 x 0.02))) were needed. We decided to include five extra patients in case some were lost to follow-up.

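### The primary model leaves out two collected variables, same-site D10 height (used only by subtraction) and tooth position; adding both is a cheap but modest improvement

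*Protocol article*

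**What the plan says.** The Primary outcome analysis section compares the one-year height loss, D365-D10, between arms in a linear mixed model with sites nested in patients. It then fixes the adjustment set: "This main analysis will be adjusted on the following prespecified variables", followed by operator team, smoking, periodontal severity, age and sex. Nothing elsewhere in the article adds to that list.

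Both absent variables are available:

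- **D10 height.** The Post-operative section states: "Baseline measurements of the crestal ridge are taken at D10 with CBCT".
- **Tooth position.** The Outcomes section has secondary comparisons "site by site (central incisor, lateral incisor, and canine").

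The Statistical methods section makes the extraction site the unit of analysis and adds that "a maximum of six teeth will be extracted per patient", so the number and mix of teeth can differ between patients. The Sequence generation section minimises on team, smoking and periodontal severity, and not on the number or type of teeth.

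**The concern.** A change score fixes the coefficient of D10 at 1. If the true slope of D365 on D10 is not 1, two things follow. Some variance that D10 could explain stays in the residual, and a chance difference in D10 between arms shifts the estimate by (slope - 1) times that difference.

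Tooth position raises a separate question. The primary outcome averages over whatever sites each patient contributes. If loss differs by tooth type and the arms happen to differ in mix, part of that difference passes into the treatment estimate. The secondary site-by-site comparisons do not correct the overall figure.

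At stake is some precision and some protection against chance imbalance in about 30 patients. The validity of the trial is not at stake.

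**Working it through.** **1. The plan's own sample size.** The Sample size section assumes that "the average 1-year resorption would be 3 mm in the control group" with SD 1.5 mm, that "2 mm of bone preservation in the test group would be clinically significant", an alpha of 5% and "a beta risk of 10" %. The Primary outcome analysis section makes tests "two-tailed, with a significance level of 0.05".

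- n per arm = 2 × (1.5 × (1.960 + 1.282) / 2)² = 11.82, rounded up to 12.
- Inflation for teams: 24 × (1 + 11 × 0.02) = 29.28, stated as 29. Adding 5 gives 34.

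The figure reproduces, and neither omitted variable enters it.

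**2. What D10 as a covariate can save.** Let s10 and s365 be the SDs at the two dates and r their correlation.

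- Variance of the change: s10² + s365² - 2·r·s10·s365.
- Residual variance with D10 in the model: s365²(1 - r²).
- Difference: (s10 - r·s365)².

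The difference is never negative. It is zero when the slope r·s365/s10 equals 1, that is, when loss is unrelated to D10. With s10 = s365 the ratio of the two variances is (1 + r)/2.

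The price of one more patient-level covariate, with 29 patients and five covariates already in the model, is approximately a factor 1 + 1/(29 - 2 - 5 - 1 - 1) = 1.05 on the variance. The article gives no r, so a range is shown:

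| r (D10, D365) | variance ratio | after cost (× 1.05) | SE ratio after cost |
|---|---|---|---|
| 0.5 | 0.75 | 0.788 | 0.89 |
| 0.8 | 0.90 | 0.945 | 0.97 |
| 0.9 | 0.95 | 0.998 | 1.00 |
| 0.92 | 0.96 | 1.008 | 1.00 |

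Break-even is at (1 + r)/2 = 1/1.05, so r = 0.905. In terms of the correlation between D10 and loss, whose square is (1 - r)/2, break-even is at about 0.22.

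For scale, take 29 patients, the 1.22 inflation and a 2 mm effect. Power is 90.2% without D10 and 96.4% at r = 0.5, before the cost of the covariate.

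**3. What tooth position can do.** The simple size of the shift is (gap in loss between tooth types) × (difference in tooth mix between arms). Neither is given. For an assumed 1 mm gap and 10 percentage points, it is 1 × 0.10 = 0.10 mm, or 5% of 2 mm. Over assumed gaps of 0.5 to 1.5 mm and mix differences of 5 to 30 points, it runs from 0.025 to 0.45 mm.

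A simulation shows how large such shifts tend to be by chance. It used 29 patients, a true effect of 2 mm, and SDs of 1.2 mm between and 0.9 mm within patients (total √(1.44 + 0.81) = 1.5), with canines losing less by the assumed gap. There were 2,000 runs per setting.

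- All six sites in every patient: adding tooth type changes nothing.
- Two to six random sites per patient: the mean estimate is about 2.0 mm with or without tooth type.

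| gap (mm) | SE without | SE with | 95th percentile of the shift in one trial (mm) |
|---|---|---|---|
| 0.5 | 0.469 | 0.468 | 0.08 |
| 1.0 | 0.481 | 0.477 | 0.14 |
| 1.5 | 0.493 | 0.487 | 0.19 |

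The SE falls by 0.1% to 1.3%. The shift reaches 4% to 10% of the 2 mm target.

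**The case against.** The strongest objection is timing. D10 comes after randomisation and grafting. The Background section says that bone and biomaterial are hard to tell apart on CBCT, and the Discussion section says that the material shows on the images after surgery. Declining to condition on such a measurement is a defensible choice. For height the objection has limited force. The planned change score already subtracts D10 in full, so any graft effect on D10 would already contaminate the planned outcome. The Discussion section also holds that remodelling cannot yet be seen at that time, and height is read to the outer buccal cortex and not to the socket contents. For width, measured across the filled socket, the objection stands.

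A second objection also stands in part. The D10 gain depends on a correlation that is not reported and on equal variances. Height is measured from a pit in the radiographic guide, and guide geometry common to both dates raises the correlation and cancels in the change. Values above 0.9 are therefore possible. The formula is also single-level, whereas treatment is compared between patients, and averaging several sites reduces the error in D10.

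A reader might infer more than the article supports:

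- **That an imbalance in starting ridge passes straight into the estimate.** It does not, because the change score subtracts D10. Only (slope - 1) times the imbalance remains.
- **That the two variables are the most predictive ones measured.** Nothing shows this. The patient factors that the article identifies as prognostic are smoking and periodontal status, and both are in the model.
- **That the plan expects loss to differ by tooth type.** It reports results by type but states no such expectation.

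**Conclusion.** The omission is real, and its consequence is modest. The planned primary analysis is valid, randomisation keeps it unbiased on average, and the sample size stands. The omission should not be read as bias or as a loss of the planned power.

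For D10, the possible saving in variance is 25% at a correlation of 0.5, 10% at 0.8 and 5% at 0.9. The net gain disappears at about 0.9, or whenever loss is unrelated to D10. This rests on equal variances and on an unreported correlation.

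For tooth position, the gain in precision is between nil and 1.3%. Its value is protection against chance imbalance in tooth mix, worth up to about 0.1 to 0.2 mm in a single trial. This rests on assumed tooth gaps of 0.5 to 1.5 mm and on patients contributing differing sets of sites.

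**What to change.** In the primary height model, prespecify two further fixed effects: tooth position (central, lateral, canine) at site level, and the D10 height of the same site. Keep the change as the outcome, so that the treatment estimate stays in mm.

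State in the plan the premise that treatment has not yet altered the D10 height, and report the model without D10 as a sensitivity analysis. For width, where the graft may affect the D10 reading, use D10 adjustment only as a sensitivity analysis.

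The cost is a short addition to the analysis plan and a few degrees of freedom in about 30 patients. No new data are needed. The adjustment relies on a measurement taken after randomisation, as the change score already does. The article lists the trial as recruiting and plans no interim analysis, so the change should be made before any outcome data are examined; afterwards it would be post hoc.

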#### Secondary outcomes analyses

The same analyses will be used to compare final loss (D365-D10) of bone ridge width, final loss of bone ridge height and width at the different extraction sites (central incisor, lateral incisor and canine) and intermediate loss (D90-D10) of bone ridge height and width.

A repeated data model will be used to compare bone loss speed between the experimental and control group.

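### The plan leaves unclear whether the supplementary unadjusted Mann-Whitney test uses sites or patients; if run on sites, as the stated unit of analysis implies, its p-values would be too small

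*Protocol article*

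**What the plan says.** Four places in the protocol article bear on this.

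- **Statistical methods** names the unit: "The unit of analysis will be the extraction site (a maximum of six teeth will be extracted per patient". It is the only sentence that does so, and it makes no exception.
- **Primary outcome analysis** makes an adjusted linear mixed (or marginal) model the main analysis. The model "will be used to account for the correlation between the different bone ridge height values in the same patient", with site at level 1 and patient at level 2. The section then adds "We will report the unadjusted analysis as well", and specifies that "mean final loss of bone ridge height will be compared between the experimental and control group by Mann-Whitney test". It also fixes the level for every test in the section: p "values will be two-tailed, with a significance level of 0.05".
- **Outcomes** describes the primary outcome as "overall (the mean of all extraction sites) mean bone ridge height loss (D365–D10) at 1 year", which suggests one averaged value per patient.
- **Secondary outcomes analyses** extends the approach: "The same analyses will be used to compare final loss" of ridge width, of height and width at each tooth type, and the intermediate losses from D10 to D90.

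**The concern.** Patients are randomised, and one allocation applies to all of a patient's sockets. A standard Mann-Whitney test assumes independent observations. The plan itself recognises that sites within a patient are correlated and protects the mixed model against this, but states no such protection for the unadjusted test.

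Two analysts could follow the text and report different p-values. One would pool all site losses in each arm, because the stated unit is the site. The other would average within patient first, because the outcome is defined as an average. The two choices also weight patients differently: by number of teeth extracted in the first case, equally in the second.

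At stake is a pre-specified p-value on the primary outcome, judged at 0.05 and printed beside the main result, and its repeats for the secondary outcomes. For a tooth type the averaging over all sites no longer applies. A patient can contribute a left and a right tooth, and the article does not say how the pair is combined.

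**Working it through.** **Inputs from the protocol article.** Two-sided level 0.05 (Primary outcome analysis); at most six sites per patient (Statistical methods); two balanced arms (Study design); 34 patients, of whom 29 are needed after inflation (Sample size).

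**Inputs not in the documents, so assumed.** The within-patient correlation of site losses (ICC), and the actual number of sites per patient, for which only the maximum is given. The ICC of 0.02 under Sample size concerns the two operator groups. It says nothing about sites within a patient.

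**Step 1: the plan's patient numbers reproduce.** With a difference of 2 mm, SD 1.5 mm and 90% power, the normal approximation gives

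n per arm = 2 × (1.96 + 1.28)² × 1.5² / 2² = 11.8, so 12.

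24 × (1 + 11 × 0.02) = 29.28, stated as 29; adding 5 gives 34. So 14 to 17 patients per arm is the right range to examine. Six sites each would give at most 29 × 6 = 174 to 34 × 6 = 204 site values.

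**Step 2: approximate type I error of a site-level test.** With m sites per patient, the variance of the arm contrast is inflated by 1 + (m − 1) × ICC. A test that ignores this has actual level

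2 × [1 − Φ(1.96 / √(1 + (m − 1) × ICC))].

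For m = 6 and ICC = 0.5 the inflation is 1 + 5 × 0.5 = 3.5. Then 1.96 / √3.5 = 1.048 and the level is 0.295.

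**Step 3: check by simulation.** Trials with no treatment effect were simulated: normal data, equal correlation between all sites of a patient, 17 patients per arm, 5,000 trials per setting.

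| ICC (assumed) | 6 sites: formula | 6 sites: simulated | 4 sites: simulated | 3 sites: simulated |
|---|---|---|---|---|
| 0.02 | 0.062 | 0.058 | 0.048 | 0.050 |
| 0.1 | 0.110 | 0.113 | 0.085 | 0.076 |
| 0.2 | 0.166 | 0.157 | 0.118 | 0.099 |
| 0.3 | 0.215 | 0.215 | 0.148 | 0.116 |
| 0.5 | 0.295 | 0.287 | 0.215 | 0.161 |
| 0.7 | 0.356 | 0.356 | 0.268 | 0.202 |

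Results with 14 patients per arm are similar (six sites: 0.101 at ICC 0.1 and 0.362 at ICC 0.7).

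**Step 4: tooth-type comparisons, m = 2.** The formula gives:

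- ICC 0.2: 1.96 / √1.2 = 1.789, level 0.074
- ICC 0.5: 1.96 / √1.5 = 1.600, level 0.110
- ICC 0.7: 1.96 / √1.7 = 1.503, level 0.133

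Simulation with 15 and 14 patients (4,000 trials per setting) gives 7%, 11% and 14%.

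**Step 5: the same test on one mean per patient.** In the Step 3 simulations, including those with 14 per arm, the level was 0.043 to 0.054 in every setting.

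**The case against.** The strongest reply is that the article never says the Mann-Whitney test is run on site values. It speaks of mean final loss, and the outcome is to "compare overall (the mean of all extraction sites) mean bone ridge height loss". Read together, these allow one mean per patient, and Step 5 shows that such a test holds its level. This stands, and it is why the point is a conflict between sections and not a proven error. It does not remove the point, because the only sentence that names a unit names the site.

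A second reply is that a condensed article may leave the aggregation step to a fuller document. That would answer mere silence. Here the article states a rule, and the rule taken literally leads to the invalid version of the test.

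A reader might go further and infer three things that the documents do not support.

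- *That the trial's main conclusion has an inflated type I error.* The main analysis is the mixed model, which accounts for within-patient correlation. The site is a legitimate level-1 unit there, and the secondary outcomes receive the same model.
- *That the unadjusted result would be significant by construction.* Even in the worst setting examined (six sites, ICC 0.7), about 64% of null trials give no significant result.
- *That severe inflation is certain.* It depends on an ICC and a site count that the article does not give. With six sites it is threefold or more from an ICC of about 0.2; with three sites, only from about 0.5; at 0.02 it is negligible.

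The documents do give reasons to expect some correlation. The Background ties the extent of resorption to the patient's profile, smoking is treated as prognostic, and all of a patient's heights are measured against one removable guide. None of this supplies a value.

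That a Mann-Whitney test gives no difference in mm is a lesser matter, since the main model supplies an adjusted one.

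**Conclusion.** The point holds as a conflict over the unit of the supplementary unadjusted test. Outcomes points to the patient, Statistical methods to the site, and Primary outcome analysis does not settle it. If the site is used, the test's type I error at a nominal 0.05 is about 0.11 to 0.36 with six sites per patient (assumed ICC 0.1 to 0.7), and about 0.07 to 0.14 with two sites (assumed ICC 0.2 to 0.7). If patient means are used, it is nominal. These figures assume normal data and equal correlation between all sites of a patient.

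Severity is moderate. A misleading p-value could appear beside the main result for the primary outcome and again for the secondary outcomes, but the main analysis and the sample size of 34 are untouched.

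**What to change.** In Statistical methods, state that the extraction site is the unit only within the mixed model, and that the patient is the unit for the unadjusted test. In Primary outcome analysis, specify that the Mann-Whitney test is run on one value per patient, namely the mean of that patient's site losses, or name a rank test for clustered data instead. In Secondary outcomes analyses, specify the mean of left and right for each tooth type where both are present.

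Optionally, report with the test the unadjusted mean difference in mm and its 95% confidence interval from the same patient-level data, so that it can be read against the 2 mm used for sizing.

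The core change is about one sentence, with a short clause for the tooth types. It needs no new data and no change to the sample size, and should be made before the data are analysed.
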